### Intervention

#### Intervention group

The participants in the intervention group will receive the CBP to increase their motivation and ability to change their dietary pattern, physical activity or smoking behavior. The CBP will be provided by nurse practitioners in the participating general practices, and will consist of a maximum of 6 individual 30-minute counseling sessions [37], followed by 3-monthly booster sessions by phone for a period of one year. The MI and PST counseling methods will be used. The counseling sessions are initially given on a weekly base, but after a few sessions the time between the sessions is extended to 2/3 weeks, followed by 3-monthly booster sessions by phone, to act as a reminder for the participants, to reinforce what they have learned, and to give them support and feedback.

One of the techniques that is used during MI is reflective listening, which is applied throughout the whole counseling process. A 'gap' between the participant's current behavior and the broader goals will be emphasized, cultivating motivation for lifestyle change. When the participant recognizes such discrepancies, a certain level of discontent arises that makes change more likely to occur. Discrepancies are emphasized after exploring the participant's views on their current and future behaviors. Rolling with resistance invites the participant to consider a new perspective, instead of having it imposed. Finally, self-efficacy, or the confidence to change a specific behavior under difficult circumstances, will be supported whenever possible because it is one of the best predictors of treatment outcome. After the MI counseling the participant is willing to change and it is time to strengthen the commitment to a plan for lifestyle change using PST. The nurse practitioner, together with the participant, will make an implementation plan concerning where, when and how the behavior changes will take place. This will be done in the following series of stages [38]: explanation of the intervention and its rationale, definition and breaking down of the problem, establishing achievable goals for problem-solving (achievable goals are SMART goals: Specific, Measurable, Achievable, Relevant, Timed), generating multiple possible solutions, evaluating and choosing the solution, implementing the preferred solution, and evaluating the outcome.

Each participant will be free to choose which lifestyle component(s) (smoking, physical activity or diet) he or she wants to change. The CBP focuses on one problem area, for which multiple sessions might be needed. MI will be used first, followed by PST when the participant is motivated. During the intervention it might be necessary to revert to MI to motivate the participant again, after which new goals can be set. The last CBP session is brought to an end by reviewing and emphasizing the entire CBP process, with emphasis on the successes achieved by the participant and implementation of CBP in the future, independent of the nurse practitioner.

#### Control group

The participants in the control group will receive written information about their risk of developing T2DM and CVD, and existing brochures containing health guidelines regarding physical activity, a healthy diet, and how to stop smoking.

Participants with a systolic blood pressure above 160 mmHg and/or hypercholesterolemia (> 8 mmol/L) will be referred to their GP for additional medication, but will remain in the study. Participants with a glucose value above 7.0 mmol/L (confirmed with a second blood sample) will also be referred to their GP and then excluded for participation.

#### Training of nurse practitioners

Prior to the onset of the study, the nurse practitioners will receive a total of 18 hours of training from experienced psychologists [name] (member of the Motivational Interviewing Network of Trainers (MINT)) and [name] (PST trainer) who are specialized in providing and co-ordinating CBPs. A treatment manual will be used during the study to guide the treatment. During the intervention the nurse practitioners will receive ongoing support during regular peer supervision meetings. Random CBP sessions will be tape-recorded to assess the adherence of the nurse practitioners to the protocol. These tape recordings will also be used in the peer supervision meetings to provide ongoing feedback and to increase uniformity of the counseling style among the nurse practitioners.

### Blinding

It is impossible to blind the participants and nurse practitioners for the intervention, but the research assistants, the principal investigator and the GPs will remain blinded during the entire intervention. This is achieved by instructing the participants not to communicate about the intervention with their GP or the medical assistants.

### Study duration

The counseling sessions will last for 2-4 months, and the total intervention period, including booster calls, will be 16 months. Together with an estimated inclusion period of 8 months, the study itself will take 24 months (2 years). The measurements will be carried out before the start of the intervention, and after 6, 12 and 24 months. The baseline measurements started on February 14^th^, 2008.

### Primary outcome measurements

- Diabetes risk score and cardiovascular risk score.

The risk of developing diabetes will be assessed by means of a risk function, calculated according to data from the ARIC Study [34] (see Additional file 1). Absolute cardiovascular risk will be assessed with a risk score, calculated according to the SCORE project [35] (see Additional file 2). For both sores and for each participant, age is set at 60 years.

### Secondary outcome measurements

- Dietary behavior, physical activity behavior, and smoking behavior.

- Cost-effectiveness and cost-utility of the CBP.

All relevant direct, indirect and total costs will be included. Costs related to diabetes, diabetic complications and cardiovascular disease are considered to be relevant. The costs of the CBP will be assessed using the bottom-up procedure, based on personnel, material and housing costs.

### Data-collection

#### Questionnaires

▪ Dietary behavior: An extended and modified version of the 8-item Food Frequency Questionnaire [39] will be used to measure the intake of fruit, vegetable, fiber, alcohol consumption and (un)saturated fat. Total energy intake can not be measured with this questionnaire.

▪ Physical activity behavior: The Short Questionnaire to Assess Health Enhancing Physical Activity (SQUASH) [40] will be used to assess physical activity within (A) commuting activities, (B) leisure time activities, (C) household activities, and (D) activities at work and school.

▪ Sedentary behavior during leisure time will be measured with a subscale of the Activity Questionnaire for Adolescents & Adults (AQUA) [41].

▪ Smoking behavior: Smoking every day/smoking now and then/never smoked/year of smoking cessation and pack years (average number packs of 20 cigarettes per day smoked, multiplied by the number of years as a smoker).

▪ Determinants of behavioral change: A 41-item questionnaire, based on existing TPB questionnaires, will be used to assess lifestyle-specific behavior with regard to the constructs attitude, social norm, self-efficacy and intention to change. To our knowledge, no suitable validated questionnaires are available. The theoretical model and questionnaires in other current studies at the research institute were used to develop this Determinants of Lifestyle Behavior Questionnaire (DLBQ).

▪ Quality of life will be assessed with the EuroQol (EQ-5D) [42,42,43].

▪ Compliance: The number of CBP sessions attended will be registered, and compliance is considered adequate if at least two sessions are attended.

#### Cost-diaries

▪ Direct health care, non-health care costs and indirect non-health care costs will be recorded in cost-diaries that will be sent via e-mail to the participants in 3-monthly time-intervals. Printed cost-diaries will be sent to participants who do not have access to or dislike the Internet. Direct health care costs will include costs of the CBP, visits to the GP, medical specialists, therapists, dieticians, medication, and hospitalization. Direct non-health care costs will include the costs of over-the-counter medication, physical activity programs, travel time, and waiting time. Indirect costs will include the costs of absence from paid and unpaid work.

▪ Co-interventions: In both groups, any co-intervention will be reported in the cost-diaries.

#### Physical measurements

▪ Anthropometric measurements: Weight, height, and waist-hip circumferences. Body weight and height will be measured to calculate the BMI (weight divided by height squared). Height will be measured to the nearest 0.1 cm without shoes, whereas weight will be measured to the nearest 0.5 kg, wearing indoor clothing and no shoes. Waist circumference will be measured at the level midway between the lowest rib margin and the iliac crest, and the hip circumference at the widest level over the greater trochanters.

▪ Systolic and diastolic blood pressure will be measured after 5 minutes of rest, in a seated position, with the Collin Press Mate (BP-8800, Komaki-City).

▪ Laboratory tests: Fasting blood samples will be taken (venapunction) to measure glucose, Hb1Ac, total cholesterol, HDL-cholesterol, and triglycerides.

### Process evaluation

A process evaluation will be carried out to study the effective and ineffective parts of the intervention. In the second questionnaire the participants of the intervention group are asked to score three items regarding their satisfaction with the intervention on a 4-point Likert scale, and indicate whether or not they are changing their lifestyle as planned in the program (yes/no). The nurse practitioners are asked to give their opinion on a 4-point Likert scale regarding five statements (i.e. about the MI and PST training and their confidence in providing the counseling sessions), and on two open-ended questions about their perception of the effectiveness of the training. These statements are scored twice: directly after the training session and again after the recruitment period (about eight months later). The quality of the nurse practitioner MI will be assessed according to the Motivational Interviewing Treatment Integrity (MITI), a behavioural coding system that will be applied to the tape-recordings of the counseling sessions [44]. The results will be linked with the risk scores of the participants after one year. This will make it possible to evaluate the effect of the counseling skills of the nurse practitioners on patient outcomes.

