### Study population

Twelve thousand inhabitants (men and women) aged 30-50 living in this region will be invited to participate in a selective screening procedure. The target group will be approached, after identification of date of birth and absence of diabetes or known CVD, from participating general practices (n = 12).

In the first step of the screening procedure the inhabitants will receive an invitation to measure their own waist circumference with a tape measure, according to detailed instructions. Waist circumference is a widely used indicator of abdominal obesity in population studies. To minimize non-response we will use the modified Tailored Design Method [32] to approach potential participants. The main elements of this approach are: a brief pre-notice postcard is sent to each of the sampled persons, and a few days later a comprehensive and easy to understand invitation is sent, together with the tape measure and a stamped addressed envelope for the reply. A week after this mailing, another postcard will be sent, in which the respondents are thanked for returning the survey questions and the non-respondents are asked to complete the waist-measurement and return it immediately. Four weeks later, a reminder and a replacement tape measure are sent to the non-respondents. Abdominal obesity is, in principle, defined as a waist circumference of 88 cm or more for women, and 102 cm or more for men [33]. All respondents with a waist circumference of 1 cm under this cut-off point or above will be invited to participate in the second step of the screening at the research center. After signing an informed consent form, this screening will include the measurement of blood pressure, a blood sample (to determine total and HDL cholesterol, triglycerides, fasting plasma glucose, HbA1c), and anthropometric measurements (height, weight, and waist and hip circumference). In addition, the participants will be given a questionnaire to fill in at home, including questionnaires about physical activity, dietary intake, smoking status, determinants of behavior according to the TPB, quality of life, and depression.

The 9-year risk of developing diabetes will be estimated using the risk function derived from data of the Atherosclerosis Risk In Communities (ARIC) Study [34], with ethnicity (black yes/no), parental history of diabetes, systolic blood pressure, waist circumference and height (Additional file 1).

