The 10-year risk of a fatal cardiovascular disease will be estimated using the formulae developed by the Systematic COronary Risk Evaluation (SCORE) project [35], with gender, smoking status, total cholesterol and systolic blood pressure (Additional file 2, see Tables 1 &2).

**Table 1 T1:** Coefficients for Eq. (1)

		CHD		Non-CHD	CVD
				
		α	p	α	p
Low risk	Men	-22.1	4.71	-26.7	5.64
	Women	-29.8	6.36	-31.0	6.62
High risk	Men	-21.0	4.62	-25.7	5.47
	Women	-28.7	6.23	-30.0	6.42

**Table 2 T2:** Coefficients for Eq. (2)

	CHD	Non-CHD
Current smoker	0.71	0.63
Cholesterol (mmol/L)	0.24	0.02
Systolic BP (mmHg)	0.018	0.022

For both scores and for each participant, age will be extrapolated to 60 years to address the problem of a high relative but low absolute risk in younger persons. This way it is possible to flag persons who will become at high absolute risk [36].

All participants with a minimum risk of 10% for developing diabetes and/or a minimum risk of 10% for CVD will be randomly assigned to either the intervention group or the control group. Exclusion criteria are: inability to communicate adequately in the Dutch language and pregnancy.

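### The second questionnaire carries items for the CBP arm only, so a completed form reveals the arm during the promised blinding period, and the stated safeguard does not cover forms

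*Protocol article*

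**What the plan says.** All references are to the protocol article.

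- **Process evaluation.** "In the second questionnaire the participants of the intervention group are asked to score three items regarding their satisfaction with the intervention". They must also "indicate whether or not they are changing their lifestyle as planned in the program (yes/no"). Control participants get neither the three items nor the yes/no item.
- **Study duration.** "The measurements will be carried out before the start of the intervention, and after 6, 12 and 24 months". The intervention, booster calls included, lasts 16 months.
- **Study population.** At screening, "the participants will be given a questionnaire to fill in at home, including questionnaires about physical activity, dietary intake, smoking status". This first questionnaire also covers behavioural determinants, quality of life and depression.
- **Secondary outcome measurements.** The behavioural outcomes are "Dietary behavior, physical activity behavior, and smoking behavior", which the Data-collection section obtains by questionnaire.
- **Study population, on SCORE.** The cardiovascular score is computed "with gender, smoking status, total cholesterol and systolic blood pressure". The ARIC score uses ethnicity, parental history, systolic pressure, waist and height.
- **Blinding.** Participants and nurse practitioners cannot be blinded, but "the research assistants, the principal investigator and the GPs will remain blinded during the entire intervention". The means is given in one sentence: "This is achieved by instructing the participants not to communicate about the intervention with their GP or the medical assistants".

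**The concern.** Two things are at stake.

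First, blinding. The trial itself asks CBP participants to write about the program on a trial form while outcome staff are meant not to know the arm. Satisfaction ratings and an answer about the program's plan can come only from a CBP participant, so the completed form amounts to an allocation record. The safeguard in the Blinding section limits what participants say, and to whom. It does not address what they write on forms.

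Second, comparability of the instrument. Self-reports of diet, activity, smoking and quality of life are compared between arms. If one arm's form also asks for a verdict on the program and a written declaration of progress, the two arms are not answering the same questionnaire. Any pull towards answers consistent with that declaration would act in one arm only.

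**Working it through.** The plan states no figure on this point, so the check sets the sections side by side.

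**1. Which questionnaire is the second one?** The first is given at screening. Measurements follow at 6, 12 and 24 months. The cost-diaries are a separate three-monthly instrument. The second questionnaire is therefore most naturally the 6-month one. This is an inference, because the Process evaluation section names no month.

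**2. Does it share a form with the outcomes?** The baseline questionnaire holds activity, diet, smoking and quality of life, and the Data-collection section lists these as questionnaire data. Calling the later form the second questionnaire implies the same series. This too is an inference, though the natural one.

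**3. Where does it fall in the blinding period?**

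| Event | Month | Relation to the 16-month period |
|---|---|---|
| Form with CBP-only items | 6 | inside, 16 − 6 = 10 months remaining |
| Follow-up visit | 12 | inside |
| Follow-up visit | 24 | outside, 24 − 16 = 8 months after the end |

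One later visit lies inside the promised period and one lies after it.

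**4. Which primary-outcome inputs could be affected?**

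- *Through an assessor who has learned the arm:* waist is measured by hand between two anatomical landmarks, so it is the most exposed. It enters ARIC only and is not a SCORE input. Blood pressure is taken with a named device and cholesterol is a laboratory value, so both are less exposed.
- *Through the participant's own answers:* smoking status is the self-reported input that can change during follow-up. It enters SCORE, and the laboratory list contains no biochemical check of it.

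**5. How sensitive is SCORE to one smoking answer?** Table 2 gives current-smoker coefficients of 0.71 (CHD) and 0.63 (non-CHD):

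- exp(0.71) = 2.03 and exp(0.63) = 1.88.
- A smoker recorded as a non-smoker therefore has the hazard multiplied by 1/2.03 = 0.49 (CHD) and 1/1.88 = 0.53 (non-CHD).
- For the CHD part, this equals 0.71/0.018 = 39 mmHg of systolic pressure.

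This shows how much one wrong answer moves one person's score. It says nothing about how many wrong answers the four items would cause.

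**6. How many participants?** At most the 300 planned for the CBP arm. The number actually identified depends on how many forms are returned completed and who reads them, which the article does not say.

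**The case against.** The strongest reply is that much of the harm depends on details the article does not give.

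- **Handling.** Nowhere does it say that research assistants or the principal investigator receive, check or enter the questionnaires. The baseline one is filled in at home, and the center has an independent administrative assistant who performs the randomization. Form routing is something an article may leave to the full protocol. This stands: a reader might infer that blinded staff will see the arm, but the text supports only that they can if they handle the form.
- **Layout.** The four items might come last or on a separate sheet, in which case they could not alter answers already given on that form. This also stands.
- **Existing bias.** CBP participants are unblinded and have already set goals and an implementation plan with the nurse practitioner, so self-report bias exists without these items. The yes/no item also permits a no. This stands: the items may add to a bias but do not create it, and the amount is unknown.
- **Process evaluation needs treated participants.** Controls have no program to rate. True, but that justifies collecting the items, not putting them in the outcome questionnaire.

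Two stronger readings are tempting. One is to assume a standardised shift in the self-reports and turn it into a false-positive rate. The documents give no such shift, so the result would only restate the assumption. The other is that unblinded waist measurement would distort both primary scores. Waist is not an input to SCORE.

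What survives is that placing arm-specific items in the second questionnaire is a stated choice, not an omission, and that the one stated safeguard does not reach it.

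**Conclusion.** The point holds in a limited form. As written, the Process evaluation section opens a route to unblinding that the Blinding section does not close, and it makes the second questionnaire differ between arms. The route opens at about month 6, with 10 months of the promised blinding still to run. It can affect the 12-month visit within that promise and the 24-month visit beyond it. It concerns at most the 300 planned CBP participants.

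The conclusion rests on two inferences: that the second questionnaire is the 6-month one, and that it also carries the self-reported outcomes. Actual unblinding further requires that blinded staff handle the form. Neither the resulting measurement bias nor any added self-report bias can be quantified from the documents. The case for acting is that the weakness is avoidable at little cost, not that a large bias has been shown.

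**What to change.** Keep the 6-month outcome questionnaire identical in both arms. Move the three satisfaction items and the yes/no item to a short separate form, sent to CBP participants only after their outcome questionnaire has been returned. Have it received and entered by someone not involved in outcome measurement; the administrative assistant who performs the randomization is one possibility. Keep it apart from the outcome data until follow-up is complete, so that the 24-month visit is protected as well. Add a sentence to the Blinding section saying how trial forms that reveal the arm are handled. If this separation is already in place, that sentence alone settles the point.

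The cost is one extra short form for about 300 people and probably a slightly lower response to the process items. No process information need be given up.

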### Sample size

In a Dutch working population of overweight people (BMI ≥ 25), which consisted of both males and females, the standard deviation of the ARIC score was found to be 8.11 [45]. For a two-sided detection of a 5% between-group difference in cardiovascular risk score, standardized at 60 years of age, with an alpha of 0.05 and a power of 90%, in the present study 120 participants will be needed in the intervention group and 120 in the control group. Assuming that 40 participants per collaborating GP are recruited, and each participant is randomized independently, this is feasible. We expect a response of approximately 65% in the first step of the screening, 20% of which will meet the abdominal obesity criterion [46,47]. Of those who meet this criterion, we expect that at least 80% will be willing to participate in the second step and the RCT (Figure 1).

A multilevel analysis is performed to be able to adjust for the clustering of observations within practices. To be able to perform stratified and multivariable analyses, and taking loss to follow-up into account, larger numbers will be needed. A total of 600 (i.e. 300 in the intervention group and 300 in the control group) is expected to suffice.

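### The sample-size paragraph pairs the SD of the diabetes score with a target difference in the cardiovascular score, and 120 per group does not follow from its stated inputs (56)

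*Protocol article*

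**What the plan says.** The Sample size section of the protocol article takes its variability from a Dutch working population of overweight people, in which "the standard deviation of the ARIC score was found to be 8.11". The next sentence states the aim of the calculation: "For a two-sided detection of a 5% between-group difference in cardiovascular risk score", standardised at age 60, "with an alpha of 0.05 and a power of 90"%. The result is that "120 participants will be needed in the intervention group and 120 in the control group".

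A feasibility remark follows: "Assuming that 40 participants per collaborating GP are recruited, and each participant is randomized independently". The next paragraph mentions multilevel analysis for clustering within practices. It then says that, for stratified and multivariable analyses and "taking loss to follow-up into account, larger numbers will be needed", and settles on 300 per group.

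Elsewhere the article keeps the two scores apart. Under Study population: "The 9-year risk of developing diabetes will be estimated using the risk function derived from data of the Atherosclerosis Risk In Communities (ARIC) Study". Cardiovascular risk is estimated with SCORE. The section on primary outcome measurements lists both scores as primary.

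**The concern.** A sample-size calculation for a difference in means needs the SD and the target difference of the same variable. Here the SD belongs to one primary outcome and the difference to the other. If the word cardiovascular is a slip for diabetes, SCORE has no power statement. If it is meant, the SD is the wrong one. Either way the paragraph needs correcting.

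The number also looks wrong. A difference of 5 with an SD of 8.11 is a standardised effect of 5/8.11 = 0.62, which does not call for 120 per group at 90% power.

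What is at stake is how the SCORE result will be read. A reader who takes the 90% at face value could treat a null SCORE finding as coming from a trial known to be well powered for it, and the article gives no basis for that.

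**Working it through.** **Inputs, all from the Sample size section:** SD 8.11 (ARIC); difference 5, read as absolute percentage points (an assumption, since the article does not say absolute or relative); two-sided alpha 0.05; power 90%; equal groups. The article gives no SD for SCORE, no intracluster correlation (ICC) and no dropout rate.

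**Attempt to reproduce 120.** n per group = 2 × (1.960 + 1.2816)² × SD² / difference² = 2 × 10.507 × 65.77 / 25 = 55.3, so 56 per group (57 by t-test), 112 in total. The stated figure is 120 per group, 240 in total.

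**Variants that might explain 120:**

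| Variant | n per group |
|---|---|
| One-sided alpha 0.05 | 46 |
| Unadjusted change score, zero correlation (SD × √2) | 111 (112 by t-test) |
| 120 read as the total | 56 (total 112) |
| Change score, two-sided alpha 0.01, 80% power | 123, but contradicts the stated alpha and power |
| Dropout inflation of 56 | reaches 120 only at about 53% loss |
| Design effect, 40 per GP, assumed ICC 0.03 | 55.29 × (1 + 39 × 0.03) = 55.29 × 2.17 = 119.97 |

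Only the last row gives 120 without contradicting a stated input or assuming an extreme loss. Its ICC is not in the article.

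**If SD 8.11 and 5 points both belong to ARIC.** At 120 per group, 5 / (8.11 × √(2/120)) = 4.776, and 4.776 − 1.960 = 2.816, which gives 99.8% power. At 300 per group power exceeds 99.9%; with a design effect of 2.17 it is still 99.9%. The difference detectable at 90% power is 8.11 × 3.2415 × √(2/n): 3.4 points at n = 120 and 2.1 points at n = 300, before loss and clustering.

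**SCORE.** No n can be computed without its SD. For a 5-point difference, 90% power requires an SD of at most 5 / (3.2415 × √(2/n)): about 11.9 at 120 per group and 18.9 at 300.

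**If 5% is relative.** The absolute difference then depends on a mean score that is not given. As an illustration at SD 8.11, a difference of 2 points needs 346 per group and 1 point needs 1,383.

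**Illustration only: how large is 5 points on SCORE?** The coefficients in Tables 1 and 2 can be used if one assumes a Weibull form with covariates centred at cholesterol 6 mmol/L and systolic pressure 120 mmHg. Neither assumption is in the article text. Take age 60, systolic pressure 135 and cholesterol 5.5 (also assumed). SCORE is then 2.9% (low-risk coefficients) or 5.2% (high-risk) in non-smoking men, 1.3% or 1.9% in non-smoking women, 5.6% or 10.3% in smoking men, and 2.5% or 3.8% in smoking women. A fall of 5 mmHg and 0.3 mmol/L moves these by 0.2 to 1.4 points. Stopping smoking moves the smokers' values by 1.2 to 5.0 points.

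**The case against.** The strongest defence is that 120 may not be a slip at all. The paragraph gives a cluster size of 40 and refers to clustering, and an ICC of 0.03 lands on 120 almost exactly. That is a fair explanation, and it means an arithmetic error is not proven. But the ICC is inferred, clustering is mentioned only after 120 has been stated, and this inflation fits poorly with randomising individuals within practices. At best, the step that more than doubles the number is undisclosed.

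A reader might infer that power is unestablished for both primary outcomes. The article does not support that: 120 is more than 56, so under the natural reading ARIC has power to spare. Its gap is an unnamed target difference.

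A reader might also set 40 per GP against the planned total, since 12 practices × 40 = 480 falls short of 600. That is a misreading. The feasibility remark follows the 120 + 120 calculation, so it supports 240, which 480 covers.

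Finally, a reader might conclude that a 5-point SCORE effect is impossible. The illustration cannot show that. It rests on an equation form, centring values and risk profiles that the article text does not give. Most of those profiles lie below the 10% cardiovascular entry threshold, although such people can enter through diabetes risk. Smoking, which the programme targets, can move an individual by about 5 points. It gives reason to justify the target and is not proof against it.

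It is also true that recruitment is 2.5 times the stated need (600/240) and that no step of the design or analysis depends on the paragraph. That limits the consequence to interpretation.

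**Conclusion.** The concern holds in a limited form. The SD and the target difference belong to different primary outcomes, so the 90% power claim is unsupported for SCORE, and no target difference is named for ARIC. Unsupported does not mean inadequate: without a SCORE SD, power for that outcome cannot be judged in either direction. The stated inputs give 56 per group (57 by t-test), not 120, provided that 5% means 5 absolute points; 120 requires an inflation that the article does not state. If SD 8.11 and 5 points both apply to ARIC, there is no shortfall. The mismatch is plain from the text and needs no assumption; the figure of 56 depends on the absolute reading of 5%.

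**What to change.** Rewrite the paragraph so that it:

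- gives an SD and an absolute target difference for ARIC and for SCORE separately, with a reason for each target; the SCORE SD can be taken from pooled, blinded baseline data;
- says whether 5% is absolute or relative;
- either replaces 120 by 56 per group for 5 points on ARIC, or states the inflation behind 120 (ICC, cluster size, loss) and why it applies under individual randomisation;
- states what 300 per group can detect at 90% power on each score: about 2.1 points for ARIC at SD 8.11 before loss and clustering, and the corresponding figure for SCORE once its SD is known.

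The cost is one paragraph and one blinded summary of baseline data. No extra participants are needed. The downside is that the stated power for SCORE may become less favourable.
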